**Table 1 Tab1:**
[figure not shown]
Schedule of enrolment, interventions, and assessments

#### Primary outcome measure

##### Vaginal palpation and visual observation: phasic fibres

The patients will be in the lithotomy position when the phasic fibres of the PFMs are evaluated; they will have their hips and knees semi-flexed and rotated externally and their upper limbs placed to the sides of the trunk. They will be asked to contract their PFMs by raising the pelvic floor musculature towards the pubic symphysis.

The patients will be instructed to perform the contractions quickly and with the maximum possible force 10 times [11]. The number of fast-twitch contractions will be determined by calculating the number of effective contractions (fast-twitch contractions with maximal force lasting 1 s each) out of 10 contractions performed.

#### Secondary outcome measures

The secondary outcome measures will be PFM function and self-efficacy in practising PFM exercises.

##### Vaginal palpation and visual observation

The lithotomy position (with the patient’s hips and knees semi-flexed and rotated externally and their upper limbs placed to the sides of the trunk) will be used to evaluate the contraction and function of the PFMs. The PFM contractions will be assessed using vaginal palpation and visual observation as follows:
For the voluntary contractions of the PFMs, the following verbal command will be provided: “squeeze the PFMs as hard as you can”. The scores will be as follows: 1 = no contractions; 2 = weak; 3 = normal; and 4 = strong.
PFM function will be assessed using the modified Oxford grading scale [0 = no contractions; 1 = flicker; 2 = weak; 3 = moderate (with lift); 4 = good (with lift); and 5 = strong (with lift)] [11].The occurrence of associated contractions of the abdominal, gluteal, and adductor muscles during the voluntary contraction of the PFMs will also be evaluated.Endurance will be evaluated based on the duration of the muscular contraction in seconds, which reflects the activity of the slow muscle fibres. Ideally, the contractions should be maintained for more than 10 s [11].

##### Self-efficacy scale for practising PFM exercises

The patients’ self-perceptions of the effectiveness of the perineal exercises will be evaluated using the self-efficacy scale for the practice of pelvic floor exercises [12]. The scale is composed of 17 questions provided in a visual analogue scale format, with responses ranging from 0 (not confident) to 100 (most confident). There are 13 questions on self-efficacy and four on the patients’ expectations of the results. The final score is obtained by averaging the scores for the items, and the total score ranges from 0 to 100, where higher values indicate greater self-efficacy/higher expectations regarding the results of training of the PFMs. The 13 questions referring to self-efficacy will be asked after the intervention period only, and the four questions regarding the expectations of the results will be asked before and after the intervention period.

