### Primary and secondary outcome measures and assessment points

The patients will be evaluated at baseline (*week 0*) and at 4 weeks post-intervention (*week T5*) (Table 1). The study population will be characterized based on sociodemographic [age, body mass index (BMI), duration of symptoms, number of pregnancies, number of vaginal deliveries, hormone therapy (HT), ethnicity, and educational level] and clinical (PFM function and self-perceptions of the effectiveness of the perineal exercises) variables.

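### The objective asks for self-efficacy before and after the intervention, but the 13 self-efficacy items have no baseline; only the 4 expectation items do

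*Protocol article*

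**What the plan says.** Under Objectives and hypothesis, the last specific objective is to compare the experimental and control groups on self-efficacy, measured with the pelvic floor exercise self-efficacy scale, both before the intervention and directly after it. Self-efficacy is a declared outcome: "The secondary outcome measures will be PFM function and self-efficacy in practising PFM exercises".

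The section Self-efficacy scale for practising PFM exercises then sets out the instrument:

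- Length: "The scale is composed of 17 questions provided in a visual analogue scale format".
- Content: "There are 13 questions on self-efficacy and four on the patients’ expectations of the results".
- Scoring: "The final score is obtained by averaging the scores for the items, and the total score ranges from 0 to 100".
- Timing of the self-efficacy items: "The 13 questions referring to self-efficacy will be asked after the intervention period only".
- Timing of the expectation items: "the four questions regarding the expectations of the results will be asked before and after the intervention period".

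Under Data analysis, a general linear model compares groups on quantitative variables that are differences between baseline and post-intervention. Where that model cannot be used, the fallback is a paired Wilcoxon test within each arm. For comparing two means, the same section provides Student's t test or, for non-Gaussian variables, the Mann-Whitney test. It does not say which of these applies to the self-efficacy scale.

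**The concern.** The objective and the data collection disagree. A before-after statement about self-efficacy needs a baseline value, and none of the items that measure self-efficacy is asked at baseline. A later analysis plan cannot repair this, because it cannot supply data that the schedule does not collect.

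The scoring rule adds a second risk. It describes one final score, an average over items, without saying that the two item sets are scored apart. An analyst who followed the objective literally would look for that score at both visits. At baseline it could only be the mean of the four expectation items. Afterwards it would be the mean of all 17, most of them self-efficacy items. The difference would then partly measure the switch of items. At stake is whether one secondary outcome can be interpreted; the primary outcome and the sample size are not affected.

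**Working it through.** **Inputs, all from the section on the self-efficacy scale.** 13 self-efficacy items (post only), 4 expectation items (pre and post), each scored 0 to 100, with the score an average of items. The plan's item count reproduces: 13 + 4 = 17.

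**What is available at each visit.**

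| | Baseline | Post-intervention |
|---|---|---|
| Self-efficacy items | 0 of 13 | 13 of 13 |
| Expectation items | 4 of 4 | 4 of 4 |
| Items in the average | 4 | 17 |

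Of the post-intervention average, 13/17 = 76% of the weight has no baseline counterpart. The remaining 4/17 = 24% has one.

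**Shift in a pooled change score with no true change.** Let E be the mean of the expectation items, taken as the same at both visits, and S the mean of the self-efficacy items.

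- Baseline score = E
- Post-intervention score = (13S + 4E)/17
- Apparent change = (13S + 4E)/17 − E = (13/17)(S − E) = 0.765 (S − E)

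The document gives neither S nor E, so the size can only be shown over an assumed range:

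| Assumed S − E | Apparent within-group change |
|---|---|
| −20 | −15.3 |
| −10 | −7.6 |
| +10 | +7.6 |
| +20 | +15.3 |

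For example, with E = 60 and S = 40 the score goes from 60 to (13 × 40 + 4 × 60)/17 = 44.7, a fall of 15.3 points although expectations did not move. If both visits use the same items, the shift is zero.

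**What happens between groups.** Write ΔS and ΔE for the post-intervention differences between arms, and ΔE₀ for the baseline difference in expectations. The between-group contrast in pooled change is

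(13/17)ΔS + (4/17)ΔE − ΔE₀.

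Randomisation makes the expected ΔE₀ zero. With no treatment effect, ΔS and ΔE are also zero in expectation and the shift cancels between arms. With an effect, the expected contrast is simply the post-intervention difference in the 17-item average. Subtracting the baseline expectation score contributes nothing to the self-efficacy part except variance. It raises the variance of the score whenever the covariance of the post-intervention score with baseline expectations is below half the variance of baseline expectations. The result looks like a change but is mostly a post-only self-efficacy difference.

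**Where the shift would enter in full.** The paired Wilcoxon fallback is run in each arm separately, so nothing cancels there.

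**The case against.** Several points on the other side carry weight.

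- **A valid self-efficacy comparison remains.** Allocation is randomised 1:1 and the objective is framed as a comparison of groups. The 13-item mean can be compared post-intervention without any baseline, using the t test or Mann-Whitney test already in Data analysis. This stands. A reader might infer that the self-efficacy objective fails altogether; the document does not support that. Only its before-after part fails, and only for the 13 items.
- **The pooled change score is nowhere prescribed.** The abstract names self-efficacy and expectations as two things, and the scale section gives each item set its own timing. Data analysis never assigns the pooled score to the difference model, and matching outcomes to tests is commonly left to a fuller document. This also stands, so the mixing of item sets is a risk that the wording leaves open and not a planned analysis. Against it, the scoring sentence speaks of one score and nothing in the article defines two.
- **A shift of 15 points overstates the damage.** A reader might infer a bias of that size in the treatment comparison. The working does not support that: the figure is a within-group shift at the edge of an assumed range, and it is expected to cancel between arms when there is no effect.
- **The averaging rule belongs to a cited instrument that is not at hand.** Agreed. That is a reason not to abolish the 17-item average, which can be computed once all items have been asked.

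The schedule in Table 1 is not shown, so the timing cannot be checked there. None of these points reconciles the objective with the timing of the 13 items.

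**Conclusion.** The point holds in a limited form. The before-after part of the secondary objective on self-efficacy cannot be met, because its 13 items are collected once; this rests on two explicit statements in the article and on no assumption.

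The second part is conditional. If the single averaged score were analysed as a change, the within-group result would shift by 0.765 (S − E) with no true change. The size depends wholly on the assumed gap between the two means. Between arms the consequence is mainly lost precision and a result that cannot be interpreted as change. The wording should be corrected before analysis, but the matter is confined to one secondary outcome.

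**What to change.** Amend the objective and the scoring text so that they agree with what is collected:

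1. Score the 13 self-efficacy items as their own mean and compare it between groups at the post-intervention assessment only, with the t test or Mann-Whitney test already planned. Compute no change score for it.
2. Score the 4 expectation items as a separate mean and compare groups using its own baseline. The difference model already in the plan will do.
3. Compute no before-after change in the pooled 17-item score. It may still be reported descriptively at T5.

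Starting to ask the 13 items at baseline would not help: Trial status reports 165 of 172 women recruited, so at most 172 − 165 = 7 could still provide one. The cost is the rewording of one objective and one outcome definition, recorded in the registry as the article provides for protocol changes. No new data are needed.

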### Trial management

The principal investigator (PI) ([name]) and a research coordinator ([name]) will regularly communicate (through emails, telephone, or in person) to promote and monitor the recruitment progress. The PI, the evaluators, and the physiotherapists will conduct conference calls or face-to-face meetings to monitor the study’s progress. All members of the research team will be informed of the progress through e-mail every 2 weeks. All the data collected will be anonymized and stored in a locked cabinet in Urogynaecology and Reconstructive Pelvic Surgery Sector at the Federal University of Sao Paulo. After each assessment and on the same day, the files will be reviewed by the research assistant to identify missing data. Any missing information will be retrieved immediately by research assistants directly from the study participants. The data will be entered weekly (depending on recruitment rate) into a computerized database, SPSS [Statistical Package for Social Sciences (SPSS Inc., Chicago, IL, EUA)], version 22.0. A final quality-control step will be performed at the time of the data analysis by the trial statistician. Frequency distributions and ranges will be analysed to detect any outliers that could signal potential errors. The data will be analysed without any nominative identifiers.

### Adverse events

In the current study, there are no anticipated risks or inconveniences, as the applied interventions and examinations are well established and widely applied in standard pelvic floor physiotherapy. All of the women will be asked during every physiotherapy and measurement consultation whether they are experiencing any adverse effects. If there are any complications or any complications are suspected, the patients will be instructed to contact a member of the study team, and they will be informed of the procedure to follow for other episodes. The Trial Steering Committee (TSC) is made up of three researchers ([name], [name], and [name]); they will meet weekly and analyse the ongoing results of the research. They will have the power to partially or completely halt the course of the study. No public organizations were involved in the development of this study.

### Statistical analysis and sample size calculation

#### Calculation of the sample size

A sample size calculation was performed to estimate the number of participants needed to obtain a statistical power of 0.80 at an alpha level of 0.05. A pilot study was previously conducted to calculate the sample size (unpublished). The results of this study showed improvements in the fast-twitch muscle fibres in both groups after the intervention. In the experimental group, the mean number of fast-twitch muscle fibres was 1.2 (± 0.7), and in the control group, it was 1.1 (± 1.7). Based on these results, we used Student’s bilateral *t* test to calculate the sample size, which was a minimum of 72 participants per group. To estimate the sample loss during the study, loss percentages from 0 to 20% were assumed. For each patient that is expected to terminate their participation in the study, two new patients will be included. Thus, considering a loss of 20%, the sample size was a minimum of 86 patients in each group.

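### The 72 per group for 80% power does not follow from the pilot figures given; those figures require about 2,650 per group, and 72 gives about 7% power

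*Protocol article*

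**What the plan says.** The subsection on calculation of the sample size in the protocol article sets out to find the number of participants "needed to obtain a statistical power of 0.80 at an alpha level of 0.05". It relies on an unpublished pilot. In the experimental group "the mean number of fast-twitch muscle fibres was 1.2", with ± 0.7; the control figure is 1.1, with ± 1.7. On the strength of these results, the authors say they used "Student’s bilateral *t* test" "to calculate the sample size, which was a minimum of 72 participants per group". Allowing for 20% loss, they raise this to at least 86 per group, which gives the total of 172 in the abstract. Allocation is 1:1 (Randomization procedures).

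The document states no other target difference and no other SD. The outcome is the primary one: the number of effective fast contractions out of 10, which the hypothesis says will be higher in the experimental group.

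**The concern.** The two pilot means differ by only 0.1 contractions, while the reported spreads are 0.7 and 1.7. A between-group t test powered at 80% for so small a standardized difference needs thousands of participants per group, not 72. Every input to the calculation is printed next to its result, so the mismatch lies within the paragraph and is not a detail deferred to another document.

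This paragraph is the only justification for the trial's size. A reader who takes the 80% at face value could treat a non-significant primary result as evidence that palpation adds nothing. At the only difference the document cites, such a result would be expected about 93% of the time even if the difference were real.

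**Working it through.** **Inputs**

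All are from the sample-size subsection, except the allocation ratio (Randomization procedures).

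- Two-sided alpha 0.05, power 0.80, Student's t test, 1:1 allocation
- Experimental group: 1.2, ± 0.7
- Control group: 1.1, ± 1.7
- Stated result: 72 per group, raised to 86 for 20% loss

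The ± values are not labelled; they are taken as SDs.

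**Attempt to reproduce the 72**

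1. Difference: 1.2 − 1.1 = 0.1.
2. Pooled SD: √[(0.7² + 1.7²)/2] = √[(0.49 + 2.89)/2] = √1.69 = 1.30.
3. Standardized difference: 0.1/1.30 = 0.077.
4. Normal approximation: n per group = 2(1.960 + 0.842)² × SD²/difference² = 2 × 7.849 × 1.69/0.01 ≈ 2,653.
5. Exact calculation with the noncentral t distribution: 2,654 per group.

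The ratio to the stated figure is 2,654/72 ≈ 37. The 72 is not reproduced.

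**Other readings (t test unless noted)**

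| Reading | n per group |
|---|---|
| SD 0.7 for both groups | 771 |
| SD 1.7 for both groups | 4,538 |
| Simple average SD, 1.2 | 2,262 |
| One-sided test, SD 1.30 | 2,091 |
| Paired comparison of the two values, correlation 0 to 1 (normal approximation) | 2,653 down to 785 pairs |
| Within-group change, experimental (1.2, SD 0.7) | 5 |
| Within-group change, control (1.1, SD 1.7) | 21 |
| Most favourable rounding: difference 0.2, SDs 0.65 and 1.65 | 619 |

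None gives 72. Even with the most favourable rounding of every printed value, power at 72 per group is only about 16%. If ± meant a standard error, the SDs, and so the required n, would be larger still.

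**Power at the stated sizes (difference 0.1, SD 1.30)**

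- 72 per group: 7.4% by noncentral t. A simulation with the two unequal SDs gave 7.6% for the ordinary t test and 7.5% for the Welch test.
- 86 per group: 7.9%.

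**What the stated sizes can detect (80% power, two-sided 5%)**

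| Evaluable per group | Standardized difference | Contractions, if SD = 1.30 |
|---|---|---|
| 86 (no loss) | 0.430 | 0.56 |
| 72 | 0.470 | 0.61 |
| 68.8 (86 × 0.80) | 0.481 | 0.63 |

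The 0.61 is about six times the pilot difference. Conversely, for 72 per group to give 80% power at a difference of 0.1, the SD would have to be 0.1/0.470 = 0.21, which matches neither printed value.

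**The case against.** The arithmetic is hard to dispute. The best counter-argument concerns what it proves. The paragraph never names a target difference, so the mismatch shows that the inputs and the result disagree, not which is wrong. A misprint is possible: a difference of 0.6 with the same SDs gives 74 per group by the normal approximation and 75 by the t test, close to 72. The 7% figure is power for 0.1 contractions out of 10, and nothing in the document says that so small a difference is the one of interest. At an SD of 1.3 the trial has 80% power for about 0.61 contractions, and the document gives no ground for calling that inadequate. With 165 of 172 women already recruited, nothing in the conduct of the trial changes.

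Much of this stands as a limit on the claim. The cause cannot be settled from the text, and it has not been shown that the trial is too small for a worthwhile effect. A misreading of a null result is a risk; no passage commits to it. A clinical rationale written now for the detectable difference would also be retrospective.

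None of it rescues the paragraph. The misprint is conjecture and does not give exactly 72. Either an input or the result must change, and as printed the claim of 80% power has no support.

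**Conclusion.** The concern holds. On the printed inputs the required size is about 2,654 per group, not 72, and power at the pilot difference is 7.4% with 72 per group and 7.9% with 86, against the stated 80%.

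This rests on reading ± as an SD, using the root-mean-square pooled SD, and comparing the two groups with a two-sided t test as the paragraph says. It does not matter whether 1.2 and 1.1 are improvements or post-treatment values, since the between-group arithmetic on them is the same. The low power applies to the printed difference of 0.1; a larger true effect would have more.

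The paragraph must be corrected, because it is the sole basis given for the size of the primary comparison.

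**What to change.** 1. Check the pilot means and SDs against the pilot data, and say what ± denotes. If a value was misprinted, print the right one together with the target difference and SD actually used, and confirm that they give 72.
2. If the values are right, delete the statement that 72 follows from them and say what the fixed size can detect. Suggested wording: *With 172 women randomised and 20% loss (about 69 evaluable per group), the trial has 80% power at a two-sided 5% level to detect a standardized difference of about 0.48, which is about 0.63 effective contractions out of 10 if the SD is 1.3.*
3. Say why a difference of that size would matter clinically, and make clear that this reasoning was added after the size was fixed.
4. State, before analysis, that the primary result will be interpreted by its 95% confidence interval against that difference, so that a non-significant result is not taken on its own as evidence of no effect.

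The cost is rewriting one paragraph and accepting a less favourable statement of what the trial can show. No additional enrolment is proposed.

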### Trial status

This study describes version 1 of the protocol (24 March 2020). This trial is actively recruiting participants (165/172). The trial is ongoing and has a planned duration of 3 years, with recruitment continuing from August 2017 to August 2020. If any changes need to be made to the study protocol, the relevant parts of the study will be updated, and the changes will be recorded in the clinical trials registry (ClinicalTrials.gov, NCT 03325543).

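### The allowance for 20% loss is miscalculated: 86 per group keeps the required 72 only up to about 16% loss, and the two-for-one sentence before it does not lead to 86

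*Protocol article*

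**What the plan says.** Everything needed is in the protocol article, under *Calculation of the sample size*. The calculation aims for "a statistical power of 0.80 at an alpha level of 0.05" with a two-sided t test, and its result is given as one "which was a minimum of 72 participants per group". For attrition, "loss percentages from 0 to 20% were assumed". A replacement sentence follows: "For each patient that is expected to terminate their participation in the study, two new patients will be included". The next sentence opens with 'Thus' and concludes that, "considering a loss of 20%, the sample size was a minimum of 86 patients in each group".

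The abstract carries the resulting total of 172. *Trial status* uses it as the recruitment target: "This trial is actively recruiting participants (165/172" enrolled at the time of writing.

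**The concern.** An allowance for loss has one purpose: the number left after the assumed loss should still meet the minimum from the power calculation. Here it does not. The base number appears to have been increased by 20% of itself, whereas the loss acts on the larger number enrolled. The two operations differ, and the one used always falls short.

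The replacement sentence adds a second difficulty. It is presented as the step that leads to 86, but two extra patients per expected loss is a larger allowance than the 14 per group actually added. The paragraph thus contains a rule and a result that do not match.

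At stake is whether the trial delivers its stated minimum at the loss it claims to cover, and whether a reader can tell how the enrolled number was reached.

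**Working it through.** **Inputs**, all from *Calculation of the sample size* unless noted:

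- minimum per group after loss: 72
- loss used for the final figure: 20%, the top of an assumed range of 0 to 20%
- enrolled per group: 86; total 172 (also in the abstract and *Trial status*)
- replacement rule: two new patients per expected loss
- power 0.80, two-sided alpha 0.05

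**1. Reproducing the plan's figure.** Base × (1 + loss) = 72 × 1.20 = 86.4, which rounds down to 86. This matches the stated number.

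**2. The number that meets the stated aim.** Base / (1 − loss) = 72 / 0.80 = 90 per group, or 180 in total. The stated 86 is 4 per group short.

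**3. What 86 delivers.**

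- At 20% loss: 86 × 0.80 = 68.8, so 68 to 69 per group remain, 3 to 4 below the minimum.
- Largest loss that still leaves 72: 1 − 72/86 = 14/86 = 16.3%.

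**4. Cost in power, assuming that 72 per group gives exactly 80%.** By the normal approximation, the standardised difference this implies is (1.960 + 0.842) × √(2/72) = 0.467. Power at n per group is Φ(0.467 × √(n/2) − 1.960):

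| n per group | Power |
|---|---|
| 72 | 0.800 |
| 69 | 0.783 |
| 68 | 0.777 |

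The cost is about 2 percentage points.

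**5. The two-for-one sentence.** Each reading is compared with 86 per group (172 in total):

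- *Literal, 20% taken on 72.* Expected losses are 0.20 × 72 = 14.4, so 2 × 14.4 = 28.8 are added and 72 + 28.8 = 100.8, about 101 per group (about 202 in total).
- *Literal, 20% taken on the number enrolled.* n = 72 + 0.4n, so n = 72/0.6 = 120 per group.
- *Two new patients meaning one per arm, for each loss across all 144.* Reaching 172 means adding 28 women, hence 14 losses, and 14/144 = 9.7%. At 20% of 144 (28.8 losses) the total would be 144 + 57.6 = 201.6.
- *One per arm, but with the 20% taken on a single group of 72.* 14.4 pairs give 86.4 per arm. This matches 86 only by leaving the other arm's expected losses out of the count.

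The 14 women added per group correspond to one-for-one replacement of 20% of 72. Apart from the last reading, which counts the losses of one arm only, none reaches 86 at 20% loss.

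**The case against.** **The shortfall is small and arises only near the end of the range.** This stands. The article assumes losses from 0 to 20%, so 20% is the upper bound. Up to 16.3%, 86 is enough, and beyond that the deficit is at most 3 to 4 women per group. But 20% is the figure the article itself attaches to 86, so that statement is wrong as printed.

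**The 78% rests on an effect the article does not state.** This also stands. The standardised difference of about 0.47 is solved backwards from 72. The printed pilot values are 1.2 (SD 0.7) and 1.1 (SD 1.7): a difference of 0.1 against a pooled SD of √((0.7² + 1.7²)/2) = 1.30, or about 0.08. At 72 per group, power for that difference is about 7%. That is a separate and larger question. Correcting the attrition step neither answers it nor depends on it, but the 78% should not be read as the trial's actual power.

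**The replacement sentence is unclear rather than plainly contradictory.** Partly so. It speaks of expected losses and can be read as a planning device. The readings give different sizes, so 101 is an illustration of the literal reading and not the one correct alternative. What remains is that 'Thus' does not follow.

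**Stronger inferences a reader might draw.** One is that the recruitment target is undefined. The article does not support that: the abstract and *Trial status* both give 172. Another is that replacement turns the analysis into one of completers. That would require the sentence to be an operating rule, which is not established. *Interventions* also provides for intention-to-treat analysis once dropouts exceed 15%, which a 20% loss would trigger.

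**Conclusion.** The point holds. The stated enrolment of 86 per group does not preserve the stated minimum of 72 at the stated loss of 20%. It does so up to about 16%, and at 20% it leaves 68 to 69. This needs no assumption beyond the article's own three numbers.

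The cost in power, from 80% to about 78%, is conditional on 72 giving 80%, which is taken as given here and not endorsed. The two-for-one sentence does not justify 86 at 20% loss and needs to be explained or removed. The size of the problem is modest: it affects how the sample size is justified, not the feasibility of the trial, and the enrolment target of 172 is clear.

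**What to change.** **Restate the attrition sentence.** Suggested wording: *Enrolling 86 women per group (172 in total) retains 72 per group with a loss of up to 16%; at a loss of 20%, about 69 per group would remain.* No patients need be added; with 165 of 172 already enrolled, an accurate statement is more practical than enlarging to 180. A power figure should not be attached to this sentence while the basis for 72 is unsettled.

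**Reconcile the two-for-one sentence with the fixed total of 172.** The sponsor knows which case applies:

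- If it was only a planning device, remove it.
- If any women were enrolled as replacements, say so and state that every randomised woman stays in the analysis.

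A blanket statement that no one is replaced should not be inserted without checking, because at this stage of recruitment it could misdescribe what was done.

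**Cost.** Two sentences, and a claim slightly less favourable than the present one.
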